## Abstract

**Background:**

HIV-infected adults initiating antiretroviral therapy (ART) in sub-Saharan Africa continue to experience high rates of morbidity and mortality during the initial months of treatment. Observational studies in high-income and resource-limited settings indicate that HIV-infected adults with low vitamin D levels may be at increased risk of mortality, HIV disease progression, and incidence of pulmonary tuberculosis (TB). As a result, vitamin D_3_ supplementation may improve survival and treatment outcomes for HIV-infected adults initiating ART.

**Methods/Design:**

The Trial of Vitamins-4 (ToV4) is an individually randomized, double-blind, placebo-controlled trial of vitamin D_3_ (cholecalciferol) supplementation conducted among 4000 HIV-infected adults with low vitamin D levels [25-hydroxyvitamin D (25(OH)D) <30 ng/mL] initiating ART in Dar es Salaam, Tanzania. The two primary aims of the trial are to determine the effect of a vitamin D_3_ supplementation regimen on incidence of (1) mortality and (2) pulmonary TB as compared to a matching placebo regimen. The primary safety outcome of the study is incident hypercalcemia. The investigational vitamin D_3_ regimen consists of oral supplements containing 50,000 IU vitamin D_3_ taken under direct observation at randomization and once a week for 3 weeks (four doses) followed by daily oral supplements containing 2000 IU vitamin D_3_ taken at home from the fourth week until trial discharge at 1 year post ART initiation. Trial participants are followed up at weekly clinic visits during the first month of ART and at monthly clinic visits thereafter until trial discharge at 1 year post ART initiation. Secondary aims of the trial are to examine the effect of the vitamin D_3_ regimen on CD4 T cell reconstitution, incidence of non-TB comorbidities, body mass index (BMI), depression and anxiety, physical activity, bone health, and immunologic biomarkers.

**Discussion:**

The ToV4 will provide causal evidence on the effect of vitamin D_3_ supplementation on incidence of pulmonary TB and mortality among HIV-infected Tanzanian adults initiating ART. The trial will also give insight to whether vitamin D_3_ supplementation trials for the prevention of pulmonary TB should be pursued in HIV-uninfected populations.

**Trial registration:**

ClinicalTrials.gov, NCT01798680. Registered on 21 February 2013.

**Electronic supplementary material:**

The online version of this article (doi:10.1186/s13063-017-1819-5) contains supplementary material, which is available to authorized users.

## Background

Access to antiretroviral therapy (ART) coverage has rapidly increased in sub-Saharan Africa during the last decade with over 12 million human immunodeficiency virus (HIV)-infected individuals on ART in 2015 [1]. In contrast to the success in expanding ART access, HIV-infected adults initiating ART in sub-Saharan Africa continue to experience significantly higher rates of morbidity and mortality during the initial months of treatment as compared to HIV-infected individuals in high-income settings [2, 3]. The 1-year mortality rate for HIV-infected individuals initiating ART in the urban Dar es Salaam, Tanzania HIV care and treatment program is estimated to be 13.1% [4]. As a result, low-cost interventions are needed to prolong and improve quality of life for HIV-infected individuals receiving ART in Tanzania and similar resource-limited settings.

Vitamin D is a potent immunomodulator with effects on both adaptive and innate immune responses which may play a prominent role in control of intracellular pathogens by enhancing cell-mediated immunity, production of antimicrobial peptides, and phagocytic activity of macrophages [5–7]. Accordingly, HIV-infected individuals with adequate levels of vitamin D may better control HIV replication and intracellular opportunistic infections as compared to individuals with suboptimal vitamin D [8]. Observational cohort studies have examined the association of vitamin D status with HIV-related morbidity and mortality in both high-income and resource-limited settings [9–17]. The largest study to date in high-income settings was conducted among a sub-sample of 1985 individuals enrolled in the EuroSIDA cohort, which consists of HIV-infected adults from 31 European countries, Israel, and Argentina [11]. The EuroSIDA vitamin D study determined individuals in the highest (>20 ng/ml) and middle (12–20 ng/mL) tertiles of 25-hydroxyvitamin D (25(OH)D) had 44% and 32% reduced risk of death as compared with individuals in the lowest tertile (<12 ng/mL), respectively [11]. To the best of our knowledge, there have been three prospective cohort studies of vitamin D conducted among HIV-infected adults in resource-limited settings [13–16]. The first vitamin D cohort study was conducted by our group among 884 HIV-infected Tanzanian pregnant women prior to availability of ART and we determined women in the highest quintile of 25(OH)D had 42% lower risk of all-cause mortality as compared with those in the lowest quintile [13]. In addition, <32 ng/mL 25(OH)D was associated with increased risk of progression to World Health Organization (WHO) HIV stage 3 or 4 disease and incidence of severe anemia, wasting, acute upper respiratory infections, and oral thrush [13]. We also more recently conducted a prospective cohort study of vitamin D among HIV-infected adult men and women initiating ART in Dar es Salaam, Tanzania [15, 16]. In this study we found individuals with vitamin D deficiency at ART initiation (25(OH)D levels <20 ng/mL) had twice the risk of mortality during the first 2 years of treatment as compared to individuals with vitamin D sufficiency (25(OH)D levels >30 ng/mL) [16]. HIV-infected adults initiating ART with vitamin D sufficiency also had reduced risk of incident pulmonary tuberculosis (TB), oral thrush, wasting, and >10% weight loss [15]. The third observational cohort study was conducted among 398 HIV-infected Ugandan adults receiving ART, which found individuals with vitamin D deficiency (<20 ng/mL 25(OH)D) had on average 65 cells/μL lower CD4 T cell counts at 18 months of follow-up as compared to individuals with vitamin D sufficiency (>30 ng/mL 25(OH)D). Overall, the observational evidence suggest HIV-infected individuals with low levels of vitamin D may be at increased risk of mortality, pulmonary TB, HIV disease progression, have poorer CD4 T cell reconstitution when on ART. Nevertheless, there are no published randomized controlled trials of vitamin D supplementation among HIV-infected adults in resource-limited settings published to date to determine causal effects.

The potential role of vitamin D in pulmonary TB immune responses has long been acknowledged as over 25 years ago Rook and colleagues published results showing the active form of vitamin D suppressed proliferation of *Mycobacterium tuberculosis* (Mtb) [18]*.* Over the past few decades, a large number of studies have examined the role of vitamin D in immune responses, particularly in macrophage function [6]. A study by Liu and colleagues found that ligation of macrophage toll-like receptor 2/1 by Mtb antigen induces expression of the vitamin D receptor and synthesis of 1,25(OH)_2_D [19]. Synthesis of 1,25(OH)_2_D by macrophages can then upregulate expression of cathelicidin, which is an antimicrobial peptide integral for killing Mtb and other intracellular pathogens [20, 21]. In addition, a landmark study by Fabri and colleagues determined vitamin D is required for an interferon-gamma (IFN-γ)-mediated antimicrobial pathway in macrophages which leads to autophagy, phagosomal maturation, and other antimicrobial activities against Mtb [5]. Generally, there is strong evidence from immunological studies suggesting that maintaining adequate levels of vitamin D may improve immune responses to TB.

There have also been a similarly large number of epidemiologic studies conducted on the relationship of vitamin D and incidence of pulmonary TB. Numerous case-control studies have determined individuals with active TB have significantly lower 25(OH)D and different genetic variants of the vitamin D receptor (VDR) as compared to healthy controls or the general population [22–26]. A recent case-control study among HIV-uninfected and HIV-infected South Africans found TB cases had about five times the odds of vitamin D deficiency (25(OH)D <20 ng/mL) as compared to population controls [27]. Nevertheless, these cross-sectional studies are prone to bias due to reverse causation since increased immune activation in individuals with active TB may lead to decreased 25(OH)D levels [6]. Only a few prospective cohort studies, which limit the potential of reverse causation, have examined the association of vitamin D and incidence of TB [15, 28, 29]. In one small prospective cohort study conducted in Pakistan, household TB contacts in the lowest tertile 25(OH)D (<7 ng/mL) had increased risk of developing TB, although these results are based on only eight incident TB cases [29]. Another small cohort study of TB contacts in Spain determined contacts with low vitamin D (<10 ng/mL 25(OH)D) had increased risk of tuberculin skin test conversion [28]. We conducted the largest prospective cohort study of vitamin D and incidence of TB to date among HIV-infected Tanzanian adults initiating ART [15]. In this study we determined individuals with 25(OH)D levels <20 ng/mL at ART initiation had approximately three times the risk of incident pulmonary TB as compared to adults with >30 ng/mL and this relationship persisted after excluding TB cases in the first 2 months of ART to effectively rule out reverse causation [15]. Overall, there is a growing base of observational evidence that HIV-infected and HIV-uninfected individuals with low vitamin D may be at increased risk of developing pulmonary TB.

Randomized controlled trials of vitamin D treatment for individuals with pulmonary TB have produced mixed findings on sputum conversion and other TB treatment outcomes; however, no randomized controlled trials of vitamin D have been conducted for prevention of pulmonary TB disease to the best of our knowledge [30]. One small randomized trial conducted in Mongolia examined the effect of vitamin D_3_ supplementation on tuberculin skin test conversion among 120 children [31]. In this trial children supplemented with 800 IU vitamin D_3_/day had about a 60% reduction in the risk of tuberculin skin test conversion during the 6 months of follow-up as compared to children randomized to placebo, but the results were not statistically significant [31]. A major barrier to conducting pulmonary TB prevention trials in the general population is the large sample size required due to low rates of TB activation (1% of those with positive tuberculin skin test per year) [32]. Nevertheless, these sample size issues are not insurmountable since incident pulmonary TB endpoints are feasible in trials of HIV-infected populations. TB activation rates are 7–10% per year in individuals with advanced HIV disease [8]. As a result, randomized controlled trials of vitamin D supplementation for TB prevention among HIV-infected individuals can be used to inform if larger and more costly trials are needed among HIV-uninfected populations, including TB contacts.

Overall, there is a growing biologic and epidemiologic evidence base which suggests HIV-infected individuals with low vitamin D levels may have increased risk of incident pulmonary TB disease and mortality; however, no randomized controlled trials of vitamin D supplementation have been published to date. In order to provide much needed causal evidence, we present the protocol for an ongoing individually randomized, parallel group, double-blind, placebo-controlled trial of vitamin D_3_ supplementation conducted among HIV-infected individuals initiating ART in Dar es Salaam, Tanzania.

## Methods/Design

The Trial of Vitamins-4 (ToV4) is an individually randomized, parallel group, double-blind, placebo-controlled trial of vitamin D_3_ (cholecalciferol) supplementation among HIV-infected adults initiating ART in Dar es Salaam, Tanzania (ClinicalTrials.gov identifier NCT01798680). The trial protocol was developed by collaborators at the Harvard T.H. Chan School of Public Health in the United States and Management and Development for Health (MDH) in the United Republic of Tanzania. The ToV4 protocol diagram is presented in Fig. 1. The schedule of trial enrollment, interventions, and assessments is presented in Fig. 2. The first participant was enrolled in the trial on 24 February 2014 and enrollment is expected to continue until March 2017 with follow-up data collection continuing until March 2018. This protocol was written following the Standard Protocol Items: Recommendations for Interventional trials (SPIRIT) checklist (see Additional file 1).

**Fig. 1 Fig1:**
[figure not shown]
Trial of Vitamins-4 (ToV4) flow diagram. *25(OH)D* 25-hydroxyvitamin D, *ART* antiretroviral therapy, *LTFU* loss to follow-up, *TB* tuberculosis

**Fig. 2 Fig2:**
[figure not shown]
Schedule of enrollment, interventions and assessments (SPIRIT figure). *25(OH)D* 25-hydroxyvitamin D

### Primary and secondary objectives

The overall goal of ToV4 is to investigate a vitamin D_3_ as a simple and low-cost intervention to prolong and improve quality of life for HIV-infected women and men who are initiating ART. The two primary aims of the study are to determine the effect of a vitamin D_3_ supplementation regimen on the hazard of incident (1) mortality and (2) pulmonary TB as compared to a matching placebo regimen during the time period of enrollment at ART initiation to discharge at 1 year of follow-up. The secondary aims of the trial are to examine the effect of the vitamin D_3_ regimen on (a) post-randomization CD4 T cell count as mean difference in cells/μL, (b) incidence of comorbidities and complications associated with HIV and/or ART, (c) post-randomization body mass index (BMI) as mean difference in kg/m^2^, (d) incidence of wasting (BMI <18.5 kg/m^2^) and >10% weight loss from baseline, (e) post-randomization depression and anxiety as mean difference in Hopkins Symptom Checklist (HSCL) scores, (f) post-randomization physical activity as mean difference in metabolic equivalents (METs), (g) post-randomization bone health biomarkers [parathyroid hormone (PTH) and alkaline phosphatase (ALP)] as mean difference in concentrations (h) post-randomization immunologic biomarkers [interlukin-2 (IL-2), interlukin-12 (IL-12), interferon-gamma (IFN-γ), and the antimicrobial peptide cathelicidin] as mean difference in concentrations and (i) risk of hypercalcemia (albumin-adjusted calcium >2.6 mmol/L).

### Study population

Individuals are eligible for the trial randomization if they meet all the following inclusion criteria: (a) adult men or women aged ≥18 years old, (b) HIV-infected, (c) initiating ART at the time of randomization, (d) have low vitamin D levels with a 25(OH)D concentration <30 ng/mL at ART initiation (e) intending to stay in Dar es Salaam for at least 1 year after enrollment, and (f) provide written informed consent. Exclusion criteria include: (a) pregnancy (women of childbearing age are required to have a negative pregnancy test within a month prior to randomization) and (b) enrolled in any other clinical trial. During the trial the ART initiation criteria for the Dar es Salaam HIV treatment program changed from CD4 T cell count <350 cells/μL or WHO HIV stage 3 or 4 disease to CD4 T cell count <500 cells/μL or WHO HIV stage 3 or 4 disease in January 2016.

### Vitamin D_3_ and placebo regimens

The investigational vitamin D_3_ trial regimen consists of oral supplements containing 50,000 IU vitamin D_3_ taken at randomization and once a week for 3 weeks at clinic visits under direct observation (four doses) followed by daily oral supplements containing 2000 IU vitamin D_3_ taken in the home starting at the fourth week until trial discharge at 1 year post ART initiation. The matching placebo regimen consists of oral placebo supplements taken at randomization and once a week for 3 weeks at clinic visits under direct observation (four doses) followed by daily oral placebo supplements taken in the home starting at the fourth week until trial discharge at 1 year post ART initiation.

We decided to use vitamin D_3_, rather than vitamin D_2_ (ergocalciferol), since vitamin D_3_ is more effective in increasing and sustaining levels of circulating 25(OH)D [33]. In addition, the two-stage vitamin D_3_ supplementation regimen was selected in order to quickly and safely boost 25(OH)D levels with the weekly 50,000 IU supplements followed by maintenance of 25(OH)D levels thereafter with the daily 2000 IU supplements. The majority of mortality for HIV-infected individuals initiating ART in resource-limited settings occurs in the first months of treatment and as a result boosting 25(OH)D levels quickly with large doses of vitamin D_3_ may produce a larger effect than daily supplements which would more gradually increase 25(OH)D over time [2]. A randomized trial using a similar two-stage regimen of weekly 50,000 IU vitamin D_3_ for 4 weeks followed by monthly 50,000 IU vitamin D_3_ maintenance doses of vitamin D_3_ among adults with primary hyperparathyroidism found 25(OH)D levels increased 19 ng/mL from baseline to 6 months and maintained levels up to 1 year [34]. We expect a similar approximately 20 ng/mL increase in 25(OH)D from randomization to 6 months. In our trial, we predict nearly all individuals in the vitamin D treatment arm will obtain 25(OH)D levels >30 ng/mL and expect no participant to exceed 85 ng/mL based on the distribution of 25(OH)D in our preliminary observational cohort study [16]. In terms of safety, vitamin D_3_ supplements containing 50,000 IU taken weekly have been found safe and effective in increasing 25(OH)D among individuals with breast cancer, multiple sclerosis, and chronic kidney disease [35–37]. Trials of 2000 IU vitamin D_3_ supplements taken daily have found the regimen maintained or slightly increased 25(OH)D overtime with very low risk of side effects [38–40].

Inclusion of a placebo control was determined to be ethical since it is not known whether the relationship of serum 25(OH)D with morbidity and mortality is causal based on evidence from observational cohort studies and it is also unknown if vitamin D supplementation starting at ART initiation can increase 25(OH)D levels during the relevant biological window to have an effect on mortality, pulmonary TB, and other treatment outcomes [15, 16]. It is also possible vitamin D supplements may have a negative effect by slowing CD4 T cell immune reconstitution due to promotion of Th2 responses, which furthers the principle of equipoise [8, 16]. In addition, a trial of vitamin D supplementation adjunct to TB treatment conducted in Guinea-Bissau found some indication of increased risk of mortality for TB/HIV co-infected participants in the vitamin D3 arm as compared with the placebo arm [41].

The vitamin D_3_ and placebo regimen for ToV4 are produced in the United States by Tischcon Corp. (Salisbury, MD). There is no discernible difference between vitamin D_3_ and placebo supplements in appearance or taste. The regimen bottles for vitamin D_3_ and placebo are also identical except for a unique participant ID label. The weekly 50,000 IU vitamin D_3_ and matching placebo supplements are single hard gelatin capsules containing a light creamy powder which weigh on average 765 mg. The weekly regimen is stored in bottles containing five capsules (one extra supplement), which are pre-labeled with the participant’s study ID. The daily 2000 IU vitamin D_3_ supplements and placebo supplements are hard gelatin capsules containing white powder which weigh on average 477 mg. The daily regimen is stored in bottles containing 35 capsules which are pre-labeled with the patient ID. The vitamin D_3_ and placebo regimens have a shelf-life of 2 years and as a result two batches are required to complete the trial. In order to monitor composition of the supplements throughout their shelf-life, Tishcon Corp. tests a random sample of capsules for the amount of vitamin D_3_ contained in each capsule by high-performance liquid chromatography (HPLC) at production and then again at the end of the shelf-life after return shipping from Tanzania. Table 1 presents the content of vitamin D_3_ and placebo supplements for the first and second regimen batches. The first batch of vitamin D_3_ and placebo supplements contained the expected amount of vitamin D_3_ at production and maintained composition for the duration of the shelf-life.

**Table 1 Tab1:** Vitamin D_3_ content of trial supplements by batch at production and at end of shelf-life as assessed by high-performance liquid chromatography (HPLC)

	Batch #1 at production (December 2013)	Batch #1 at end of shelf-life (September 2015)	Batch #2 at production (November 2015)	Batch #2 at end of shelf-life
50,000 IU Vitamin D_3_	50,949 IU (101.9%)	48,210 IU (96.4%)	52,325 IU (104.7%)	Currently in use
Matching Placebo for 50,000 IU	None detected	None detected	None detected	Currently in use
2000 IU Vitamin D_3_	2076 IU (103.8%)	2103 IU (105%)	2162 IU (108.1%)	Currently in use
Matching Placebo for 2000 IU	None detected	None detected	None detected	Currently in use

### Sample size

Sample size and power calculations for ToV4 assumed 1:1 randomization to vitamin D_3_ and placebo arms, a nominal Type I error rate (alpha) of 0.05 and a 10% loss to follow-up rate. Due to the possibility of improved care, increased CD4 T cell thresholds for ART initiation and expanded use of isoniazid preventive therapy (IPT) overtime, we selected a trial sample size of 4000 individuals that would provide adequate power for a range of mortality and pulmonary TB rates. Power for the binomial outcomes of mortality and pulmonary TB were calculated based on a two-sided two-sample test for proportions. Assuming a total sample size of 4000 individuals, Table 2 shows the power to detect a range of relative risks for mortality and pulmonary TB for the vitamin D_3_ arm compared with the placebo arm with varying cumulative incidence of mortality and pulmonary TB in the placebo arm. In terms of the mortality endpoint, the ToV4 with an expected sample size of 4000 will have excellent power to detect a relative risk of 0.70 or less (≥90% power), even if the 1-year incidence of mortality in the placebo group decreases to 10% (90% power). A sample size of 4000 will also have 85% power to detect a relative risk of 0.75 if the 1-year mortality rate is 12.5%. This range of detectable effect sizes for mortality is reasonable based on our preliminary observational cohort study which found a 50% increase in risk of mortality among HIV-infected individuals initiating ART with vitamin D deficiency as compared to sufficiency [16]. The cumulative incidence of pulmonary TB during the first year of ART among HIV-infected adults enrolled in ART programs in Africa varies between 5 and 10% [42]. The ToV4 with a sample size of 4000 has excellent power (>85%) to detect relative risk 0.60 or less and has good power (>79%) to detect a relative risk of 0.70 if the incidence of pulmonary TB in the placebo arm is greater than 7.5%. This range of detectable effect sizes for pulmonary TB is also reasonable given our observational study of HIV-infected adults initiating ART determined individuals with vitamin D deficiency had 2.89 (95% CI: 1.31–7.41) times the hazard of incident pulmonary TB as compared to vitamin D sufficient individuals [15].

**Table 2 Tab2:** Statistical power for a trial sample size of 4000 with 1:1 randomization to vitamin D_3_ and placebo arms, a nominal Type I error rate (alpha) of 0.05 and a 10% loss to follow-up rate

*Mortality*			
	Relative risk of mortality		
Cumulative 1-year incidence mortality in placebo arm	RR = 0.75	RR = 0.70	RR = 0.65
10%	76%	90%	97%
12.5%	85%	95%	99%
15%	91%	98%	99%
*Pulmonary tuberculosis (TB)*			
	Relative risk of pulmonary TB		
Cumulative incidence pulmonary TB in placebo arm	RR = 0.70	RR = 0.65	RR = 0.60
5%	61%	75%	86%
7.5%	79%	90%	97%
10%	90%	97%	99%

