### Statistical analysis plan

An intent-to-treat analysis will be used as the primary analytic strategy for all analyses. The primary efficacy trial endpoints for this trial are (1) death and (2) incident pulmonary TB. The primary safety endpoint is hypercalcemia (albumin-adjusted calcium >2.6 mmol/L). We will use the use the log-rank test to test the differences in the incidence rates of death and pulmonary TB between the treatment arms, and use the Fisher’s exact test to test differences in proportion of participants with incident hypercalcemia.

The secondary endpoints for the study include: (a) post-randomization CD4 T cell count, (b) incidence of comorbidities and complications associated with HIV and/or ART, (c) post-randomization BMI, (d) incidence of wasting (BMI <18.5 kg/m^2^) and >10% weight loss from baseline, (e) post-randomization depression and anxiety scores as assessed by the Hopkins Symptom Checklist (HSCL), (f) post-randomization physical activity as measured by METs, (g) post-randomization bone health biomarker levels (PTH and ALP) and (h) post-randomization immunologic biomarker levels (IL-2, IL-12, IFN-γ, and cathelicidin). We will use linear mixed-effects models with a random intercept, a compound symmetric covariance structure, and robust standard errors to assess mean differences between baseline and post-randomization levels of CD4 T cell count, BMI, METs, 25(OH)D, PTH, ALP, IL-2, IL-12, IFN-γ, and cathelicidin by randomization group. Linear mixed-effects models will lead to robust inference for the fixed effects even if the covariance structure is misspecified. Linear mixed-effects models will also account for within-subject correlation, and accommodate varying number and timing of measurements per participant over time. We will use a generalized linear mixed model with random intercept, a compound symmetric covariance structure, and robust standard errors to assess differences in the incidence of comorbidities and complications associated with HIV and/or ART which are repeatable binomial events. The log-rank test will be used to assess differences in the incidence rates of wasting and >10% weight loss between the treatment arms.

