Overall, the ToV4 will provide causal evidence if vitamin D_3_ should be considered as an ART adjunct intervention to reduce pulmonary TB and mortality among HIV-infected adults initiating treatment. The trial will also provide evidence for the effect of vitamin D_3_ supplementation on a wide range of secondary outcomes including: CD4 T cell reconstitution, non-pulmonary TB comorbidities and complications associated with HIV and/or ART, bone health, immunologic biomarkers, weight gain, depression and anxiety, physical activity, and incidence of hypercalcemia. The results of the trial are likely generalizable to HIV-infected adults with low vitamin D who are initiating ART in similar resource-limited settings and the trial findings will also inform whether larger vitamin D_3_ supplementation trials for the prevention of TB in HIV-uninfected populations should be pursued.

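### Table 2 gives the full two-sided 0.05 to each of two primary endpoints, and the article states no rule for judging the two together

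*Protocol article*

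**What the plan says.** The Statistical analysis plan section of the protocol article names two endpoints on an equal footing: "The primary efficacy trial endpoints for this trial are (1) death and (2) incident pulmonary TB". It assigns the log-rank test to "test the differences in the incidence rates of death and pulmonary TB between the treatment arms". It gives no significance level for either test and no rule that links them.

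The Sample size section sets the error rate for the power calculation, "a nominal Type I error rate (alpha) of 0.05 and a 10% loss to follow-up rate", and the method: "Power for the binomial outcomes of mortality and pulmonary TB were calculated based on a two-sided two-sample test for proportions". Table 2 then lists nine cells for mortality and nine for TB under the same heading, and the text draws a separate power conclusion for each endpoint. The Discussion says that the trial will "provide causal evidence if vitamin D_3_ should be considered as an ART adjunct intervention to reduce pulmonary TB and mortality".

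**The concern.** Two primary tests at 0.05 each give two chances of a false positive. If a significant result on either endpoint would be reported as a primary success, 0.05 is the error rate of one test and not of the trial's primary claim. A reader who meets one p-value between 0.025 and 0.05, with the other endpoint null, would then take the evidence to be stronger than it is.

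The power figures are affected too. They were computed with the whole 0.05 for each endpoint. A rule that holds the joint error at 0.05 leaves less for at least one of them, so the printed power cannot apply across the whole table.

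**Working it through.** **Inputs from the Sample size section and Table 2.** Total 4000, allocated 1:1, with 10% loss: 2000 × 0.9 = 1800 per arm. Two-sided alpha 0.05, two-sample test of proportions.

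**Step 1: reproduce Table 2.** With p1 the placebo risk, p2 = RR × p1 and p̄ their mean,

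power = Φ{ [ (p1 − p2) − z·√(2p̄(1 − p̄)/n) ] / √([p1(1 − p1) + p2(1 − p2)]/n) }

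- Mortality 10%, RR 0.70: difference 0.030, null SE 0.009296, alternative SE 0.009283. With z = 1.960: (0.030 − 0.018220)/0.009283 = 1.269, power 89.8% (stated 90%).
- TB 7.5%, RR 0.70: difference 0.0225, SEs 0.008144 and 0.008135. (0.0225 − 0.015961)/0.008135 = 0.804, power 78.9% (stated 79%).

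All 18 cells agree within 1 point. Table 2 therefore gives the full 0.05 to each endpoint.

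**Step 2: joint error with both tests at 0.05 and no effect on either.** Under independence: 1 − 0.95² = 9.75%. With correlated test statistics: 1 − P(|Z1| < 1.96 and |Z2| < 1.96). The article gives no correlation, so a range is shown.

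| Assumed correlation | Familywise error |
|---|---|
| 0 | 9.75% |
| 0.2 | 9.6% |
| 0.5 | 9.1% |
| 0.7 | 8.3% |
| 0.9 | 7.0% |

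**Step 3: power at 0.025 per endpoint.** Same formula with z = 2.241. For mortality 10%, RR 0.70: (0.030 − 0.020836)/0.009283 = 0.987, power 83.8%. For the four cells that the text relies on:

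| Cell | Stated | Recomputed at 0.05 | At 0.025 |
|---|---|---|---|
| Mortality 10%, RR 0.70 | 90% | 89.8% | 83.8% |
| Mortality 12.5%, RR 0.75 | 85% | 85.2% | 77.7% |
| TB 7.5%, RR 0.70 | 79% | 78.9% | 69.9% |
| TB 5%, RR 0.60 | 86% | 86.5% | 79.4% |

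The largest fall elsewhere is TB 5%, RR 0.70: stated 61%, recomputed 60.7%, and 49.6% at 0.025, about 11 points.

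**Step 4: power under less costly rules.** Take mortality 10%, RR 0.70 and TB 7.5%, RR 0.70, both effects real.

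- Hochberg declares an endpoint significant if its p ≤ 0.025, or if both p ≤ 0.05. Under independence, mortality is 0.838 + (0.898 − 0.838) × 0.789 = 88.5%, and TB is 0.699 + (0.789 − 0.699) × 0.898 = 78.0%. At an assumed correlation of 0.2, simulation gives about 88% and 78%. Simulated error with no effect on either endpoint is 4.8% to 5.0%.
- Fixed sequence with mortality first: mortality keeps 89.8%, and TB falls to 0.898 × 0.789 = 71% under independence.
- Both required: the trial succeeds with probability 0.898 × 0.789 = 71% under independence.

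**The case against.** The strongest reply is that nothing in the article is false. It calls 0.05 nominal, the usual word for a per-test level, and never claims a trial-wise rate. A multiplicity rule commonly sits in the full protocol or analysis plan, which is not shown. The two aims are numbered separately, and whether to control error jointly over distinct questions is a matter on which statisticians differ.

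Much of this stands, and it rules out four stronger readings that a reader might infer:

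- **That both endpoints will be tested at 0.05.** The level appears only in the power section. The analysis section gives none for the log-rank tests.
- **That the chance of a false primary claim is nearly 10%.** The 9.75% is the value at independence, and it needs a rule that either endpoint suffices. The Discussion sentence joins TB and mortality with an and, and does not settle either versus both. If both had to succeed, there would be no inflation. Positive correlation is plausible, because TB can cause death, and it lowers the figure.
- **That Table 2 holds only without error control.** A fixed sequence keeps the first endpoint's figures in full, and Hochberg nearly keeps both when both effects are real.
- **That no rule exists.** The unseen plan may contain one.

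What the reply does not answer is the stated power. If an unseen plan controls the joint error, some Table 2 figures and the text drawn from them do not describe the planned tests. If no plan does so, the table rests on unadjusted tests and should say so.

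**Conclusion.** The point holds in conditional form. Table 2 assigns an unsplit two-sided 0.05 to each of two primary endpoints, and the article states no rule that links them. If either endpoint alone supports a claim and each is judged at 0.05, the joint error lies between 7.0% and 9.75% for assumed correlations from 0.9 down to 0. No rule that controls that error preserves the whole table, since declaring each endpoint whenever its p ≤ 0.05 is the uncontrolled rule itself. The worst-case loss in the four cells used in the text is 6 to 9 points. It takes mortality at 10% and RR 0.70 below 90%, TB at 5% and RR 0.60 below 85%, and TB at 7.5% and RR 0.70 to about 70%.

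This should be corrected, but it does not undermine the design. The assumptions are the either-endpoint claim rule, testing at the level used for power, and the correlation range. The power figures use the article's own test of proportions.

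**What to change.** Unless the full analysis plan already sets a rule, state before unblinding that the two primary log-rank tests are judged by the Hochberg procedure: both are significant if both p ≤ 0.05; otherwise an endpoint needs p ≤ 0.025. If the plan already has a rule, cite it and restate the power to match.

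In Table 2, add power at 0.025 as the worst case and label the present figures as unadjusted. Amend the power statements in the text accordingly.

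The cost is one sentence and a restated table, with no added patients. For the pair of effects worked above, Hochberg costs about 1 to 2 points if both are real and the tests are independent or weakly correlated. The loss can never exceed the fall to the 0.025 figures. If only one effect is real, the loss approaches that fall: 6 to 9 points in the cells quoted in the text, and up to about 11 elsewhere. Other controlling rules are open to the sponsor. A fixed sequence protects the first endpoint fully but makes the second depend on it.
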